#### **Variables**

##### Independent variables

Counselling intervention activity based on shared decision making in the birth plan

Delivery of information leaflet: yes, no

### Sociodemographic and obstetric variables

- Nationality: country of origin.
- Age calculated from the date of birth, years, and months.
- Educational level: without studies; primary studies; secondary studies; university studies.
- Employment: yes, no.
- Live with your partner: yes, no.
- Previous births: yes, no.
- Maternal education: yes, no.
- Internet use for seeking information: yes, no.

### Outcome variables

#### Variables related to the birth plan

- Presentation of the birth plan to the hospital: yes, no.
- Reasons of non-presentation to the birth plan: I did not think it was necessary, I forgot, the professionals who attended me did not ask me, others.
- Usefulness of completing the birth plan in decision-making on aspects of childbirth. On an interval scale from 1 to 5. 0 is not useful at all and 5 is very useful.
- Sufficient information received during the pregnancy about the birth: yes, no
- Use of the birth plan in the next pregnancy: yes, no
- Common preferences on aspects of childbirth expressed in the birth plans: yes, no.
- Companion.
- Physical space: unique space, light graduation.
- Comfort measures and support for childbirth: listen to music, birthing ball.
- Drink fluids during labour.
- Foetal monitoring: continuous, intermittent.
- Freedom of movement.
- Pain relief methods: try labour without anaesthesia, epidural, relaxation techniques, breathing techniques, massage, others non-pharmacological

alternatives methods.

- Birth: directed pushing, spontaneous pushing, choose birthing position, use of the mirror for the birth,
- Baby: Early skin to skin in the delivery room, delayed clamping of the umbilical cord, breastfeeding delivery room, I do not want to breastfeed, consult my opinion before giving food to the baby
- Change of preferences regarding aspects of childbirth.

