## **Objectives**

To evaluate the effectiveness of a counselling intervention in the birth plan, based on “shared decision-making”, in pregnant women in relation to the presentation of the birth plan to the hospital and on preferences regarding aspects related to childbirth and satisfaction with the childbirth, compared to the standard counselling.

To evaluate the effectiveness of a counselling intervention in the birth plan, based on “shared decision-making”, in pregnant women in relation to the degree of information received in the pregnancy about the childbirth, with respect to the standard counselling

**Design.** A cluster randomised trial study, multicentre, parallel which will reveal the effectiveness of counselling intervention birth plan will be held based on "shared decision-making".

**Participants:** Pregnant women with prenatal care in Sexual and Reproductive Health Care (ASSIR) centres and who wish to participate in the study. Sample size: 266 pregnant women will be studied, 133 in each of the groups.

**Statistical analysis:** Descriptive analysis will be performed in all the variables and a bivariant analysis through hypothesis testing. Confidence interval CI will be settled on 95%. A multivariate analysis, relative risks with a CI of 95%.

**Keywords:** birth plan, assessment, midwives, satisfaction, shared decision making.

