## **HYPOTHESIS**

- Counselling on the birth plan for pregnant women, based on "shared decision making" will increase the presentation of birth plans to the hospital.
- Counselling on the birth plan for pregnant women, based on “shared decision-making” will modify: preferences on aspects related to childbirth, the degree of satisfaction with the information received in the pregnancy on the childbirth and the degree satisfaction in childbirth, in relation to the pregnant women who receive the usual counselling

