## **OBJECTIVES**

### **Main objectives**

To evaluate the effectiveness of a counselling intervention in the birth plan, based on “shared decision-making”, in pregnant women in relation to the presentation of the birth plan to the hospital, the preferences regarding aspects related to childbirth and satisfaction with the childbirth, compared to the standard counselling.

To evaluate the effectiveness of a counselling intervention in the birth plan, based on “shared decision-making”, in pregnant women in relation to the information received during the pregnancy about the childbirth, with respect standard counselling.

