### **Secondary objectives**

- 1.- Describe the pregnant women's sociodemographic and obstetrics characteristics.
- 2.- Analyse if there are differences between the pregnant women of both study groups in the preferences regarding: companion, physical space, delivery procedures, pain relief methods, second stage of birth, the baby and breastfeeding.
- 3.-Find out the perception of pregnant women on the degree of usefulness of the preparation of the birth plan.
- 4.- To find out the degree of global satisfaction of pregnant women in childbirth, satisfaction in decision-making in first and second stage childbirth in pregnant women in both study groups.

5.-Determine the reasons for non-presentation of the birth plans to the hospitals of the pregnant women in both study groups.

6. Find out if there are differences, according to the sociodemographic and obstetric characteristics of the pregnant women, in the presentation of birth plans to the hospital, in the preferences of aspects related to childbirth, the degree of information received in the pregnancy about the childbirth and in satisfaction in childbirth in both study groups.

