#### **Data collection and tools**

Birth plan. It is the document included in the Protocol for natural assistance to normal childbirth of the Catalan Health Department . It consists of items grouped into sections that refer to preferences about companion, physical space, procedures, pain relief methods, aspects related to first and second stage of birth, postpartum and lactation. The woman completes the birth plan and can choose more than one option

in each section. The birth plans are agreed upon between ASSIR and the referral hospital according to the specific characteristics of each Hospital.

MacKey Childbirth Satisfaction Scale. Questionnaire validated into Spanish with an interclass coefficient of 0.93 for the global scale and with a Cronbach's alpha reliability greater than 0.7 in all subscales . It consists of 35 items. Each item is valued on a Likert scale, 1 as very dissatisfied, 2 not very satisfied, 3 indifferent, 4 satisfied, 5 very satisfied. The global score is obtained by adding the values assigned to each item. A higher score means greater satisfaction.

Sociodemographic and obstetric data sheet. Prepared by the research team, it consists of sociodemographic data and variables related to childbirth.

Presentation of the birth plan to the hospital data sheet. It consists of four closed questions: received enough information on the pregnancy about the birth, presented the birth plan to the hospital, if not, what was the cause, a useful question of completion of the birth plan in the decision-making in the childbirth that was valued on a scale of 0 to 5, and a question if they would use the birth plan in the next pregnancy.

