### **Data collection procedure**

The midwives of the ASSIR will carry out the recruitment of the pregnant women in the control and intervention group in the prenatal visit of 24-28 weeks of gestation and they will be explained what the study consists of verbally and in writing. If they wish to participate, the informed consent will be collected and then the midwife will collect the sociodemographic and obstetric data and will deliver the birth plan for the pregnant women to fill in at home.

In the prenatal visit of 29-33 weeks of gestation, midwives will collect the completed birth plans and will deliver a new birth plan that the women will fill out at home and will be instructed to deliver a copy at the prenatal visit between the 34-40 weeks of gestation.

The midwife will keep a copy and will indicate to the pregnant women that the original must be presented to the hospital. In the women in the intervention group, the midwives will carry out the standardized counselling intervention in the preparation of the birth plan based on the shared decision making of Epstein et al and in the pregnant women in the control group, the midwives will carry out the usual practice of counselling the plan of birth.

In the postpartum visit between hospital discharge and the 6th postpartum week, the midwives of the control and intervention group will collect the childbirth data and deliver an sealed envelope with the questionnaire of questions about the childbirth and the birth plan, sufficient information satisfaction received during pregnancy about the delivery, usefulness of completing the birth plan, intention to use it in the next pregnancy and the MacKey questionnaire on the satisfaction of childbirth.

**Pilot test.** A pilot test will be carried out with 10 pregnant women in each ASSIR.

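### The hypothesis on satisfaction with information is graded, but the only information measure is one yes/no sufficiency item, which can answer the main objective as worded in the body but not that hypothesis

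*Protocol*

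**What the plan says.** The protocol words the information construct in several ways:

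- **Hypothesis:** counselling will modify "the degree of satisfaction with the information received in the pregnancy on the childbirth".
- **Abstract, second objective:** effectiveness is judged "in relation to the degree of information received in the pregnancy about the childbirth".
- **Main objectives, second objective:** effectiveness is judged "in relation to the information received during the pregnancy about the childbirth", with neither degree nor satisfaction.
- **Secondary objectives, item 6:** differences by women's characteristics are sought in, among other things, "the degree of information received in the pregnancy about the childbirth".

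The measurement side is a single binary item. The outcome list gives "Sufficient information received during the pregnancy about the birth: yes, no". Data collection and tools describes it as a closed question on the presentation data sheet, on whether the woman "received enough information on the pregnancy about the birth". Data collection procedure has the questionnaire handed over "In the postpartum visit between hospital discharge and the 6th postpartum week", and there describes the content as "sufficient information satisfaction received during pregnancy about the delivery", which merges sufficiency and satisfaction.

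**The concern.** A yes/no answer on sufficiency contains no degree, and it does not ask about satisfaction. The hypothesis therefore has no variable that can test it as written. A statistical analysis plan cannot repair this, because no analysis recovers a gradation that the form never collected.

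The construct is not peripheral. Information is the whole of the second main objective, and the intervention consists largely of explaining evidence, giving a leaflet and checking understanding. A move from just adequately to fully informed is a plausible effect of such counselling, and this item would record it as no change. The inconsistent wording also leaves open which result the investigators would report as answering the objective.

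**Working it through.** **1. Construct against instrument.**

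| Place in the protocol | Construct | Does the yes/no item answer it? |
|---|---|---|
| Hypothesis | graded satisfaction with information | No |
| Abstract, second objective | graded amount of information | No |
| Secondary objective 6 | graded amount of information | No |
| Main objectives, second objective | information received, ungraded | Yes, as a proportion |

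**2. Does another listed measure fill the gap?** The MacKey scale concerns satisfaction with childbirth, and the protocol names only its total and the decision-participation subscales for use. The usefulness item concerns completing the birth plan. No other listed variable grades information or satisfaction with it.

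**3. Room to show a benefit.** The Background section cites a 2016 Catalan survey in which 64.2% reported sufficient information on birth. If control women resemble that survey (an assumption), 100 − 64.2 = 35.8% could move from no to yes. Any improvement in the rest is invisible to the item.

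**4. Illustrative loss of information.** The protocol states no power, effect size or distribution for this outcome, so there is no figure to reproduce. The figures below rest on assumed scales and, except where stated, treat women as independent.

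- *Against a continuous normal trait.* Relative efficiency = φ(z)²/[p(1−p)]. With p = 0.642, z = 0.364 and φ(z) = 0.373, this is 0.1394/0.2298 = 0.607. It is 0.637 at a 50% split and 0.490 at an 80% split.
- *Against a five-level item under proportional odds.* Information is proportional to 1 − Σp³. For yes/no it is 3 × 0.642 × 0.358 = 0.690. For an assumed spread of 8/13/15/40/24% it is 1 − 0.084 = 0.916. The ratio is 0.690/0.916 = 0.75.
- *Power for an assumed shift of 0.35 SD (two-sided 5%).* The yes rate moves from 64.2% to Φ(0.364 + 0.35) = 76.2%. The five-level figures come from simulation with a Wilcoxon test and assumed cut points, with the sufficiency cut kept at 64.2%.

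| Women per arm | Yes/no | Five-level | Continuous |
|---|---|---|---|
| 133 | 57% | 73% | 81% |
| 113 (133 × 0.85, after 15% loss) | 51% | 66% | 75% |

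- *Smallest difference detectable with 80% power on the yes/no item.* It is 15.4 points (64.2% to 79.6%) with 133 per arm, and 16.6 points (to 80.8%) with 113.
- *Effect of clustering on the comparison.* Four units are randomised, so 266/4 = 66.5 women per cluster. Dichotomising shrinks the intracluster correlation by about the same factor, 0.607. Relative efficiency against the continuous trait becomes 0.607 × (1 + 65.5ρ)/(1 + 65.5 × 0.607ρ). For assumed latent ρ of 0.01, 0.02 and 0.05 this is about 72%, 78% and 87%. Clustering lowers every power figure above but narrows the gap between the measures.

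**The case against.** The strongest reply is that the binary item was a reasoned choice. The Background section motivates the study with the percentage of women who had sufficient information, and the item uses the same metric. The Analysis section plans chi-square tests and relative risks, which suit a binary outcome. Sufficiency is a threshold, and raising the proportion who reach it is a legitimate aim. All of this stands, and it is why the item should be kept. It does not give the hypothesis a measure.

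Three stronger readings are tempting, and the protocol supports none of them.

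- *The second main objective cannot be answered.* A reader who relies on the abstract might infer this. The version under Main objectives omits degree and satisfaction, and a proportion answers it.
- *The trial loses a quarter to two fifths of its effective sample.* The 75% and 61% figures depend on an invented category spread or an assumed normal trait, and they ignore clustering and the 15% loss. The 61% compares the item with a perfectly measured continuous trait, which is not what would replace it. The sample size rests on presentation of the birth plan alone.
- *Control women are at a ceiling.* The 64.2% comes from a Catalonia-wide survey, not from control women in these centres, and it leaves about 36 points of room.

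Asking the question after the birth is not shown to be a fault in itself.

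**Conclusion.** The mismatch is real and rests on the protocol's text alone. A graded hypothesis, together with the abstract's second objective and secondary objective 6, is paired with one yes/no sufficiency item, and the data collection text blurs sufficiency with satisfaction. The item answers the main objective as worded in the body. It does not answer the hypothesis, and it is blind to gains among women who would already say yes.

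The size of any loss of power is not established. About 75% of the information of a five-level item, or 61% of a continuous one, is an illustration under the assumptions above. The primary comparison and its sample size are untouched. The point deserves correction because the repair is cheap before the forms are used and impossible once they have been completed.

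**What to change.** 1. Keep the yes/no sufficiency item. It answers the objective in the body and preserves comparability with the 2016 survey.
2. Add to the same postpartum questionnaire one 1-5 rating of satisfaction with the information received in pregnancy about the birth, using the response anchors the protocol already gives for the MacKey scale. List it among the outcome variables and on the data sheet, and name it as the outcome for the hypothesis.
3. Do not derive sufficiency by grouping ratings of 4-5. A satisfied woman is not necessarily a sufficiently informed one.
4. Align the abstract's second objective, the second main objective and secondary objective 6 with whichever item answers each. A satisfaction rating does not measure the amount of information received, so references to a degree of information should become either the proportion sufficiently informed or the satisfaction rating. Separate the two constructs in Data collection procedure.

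The cost is one more question for the woman and one more outcome to report. If the forms are already in use, what remains is to reword the hypothesis and objectives to the proportion reporting sufficient information. That removes the contradiction but not the blindness to gains above the threshold.

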#### Obstetric variables:

- Onset of labour: spontaneous, induced
- Type of birth: spontaneous vaginal, operative birth, caesarean section
- Episiotomy: yes, no.
- Type of analgesia: non-pharmacological, pharmacological, both.
- Non-pharmacological analgesia: relaxation, breathing techniques, massage, use of water, local heat, birthing ball, TENS, others: acupuncture, aromatherapy, homeopathy, Bach flowers.
- Pharmacological: epidural
- Early of skin to skin in the delivery room: yes, no.
- Initiation of breastfeeding in the delivery room: yes, no.
- Perinatal complications: no, yes.
- Maternal complications: no, yes.

#### Satisfaction with the childbirth experience

- Satisfaction in childbirth. Using the MacKey scale of satisfaction at childbirth . On a scale of 1 to 5. 1 very dissatisfied, 2 not very satisfied, 3 indifferent, 4 satisfied, 5 very satisfied. The total score on the scale and on the subscales of degree of participation in decision-making in dilation and delivery will be considered.

#### **Data collection and tools**

Birth plan. It is the document included in the Protocol for natural assistance to normal childbirth of the Catalan Health Department . It consists of items grouped into sections that refer to preferences about companion, physical space, procedures, pain relief methods, aspects related to first and second stage of birth, postpartum and lactation. The woman completes the birth plan and can choose more than one option

in each section. The birth plans are agreed upon between ASSIR and the referral hospital according to the specific characteristics of each Hospital.

MacKey Childbirth Satisfaction Scale. Questionnaire validated into Spanish with an interclass coefficient of 0.93 for the global scale and with a Cronbach's alpha reliability greater than 0.7 in all subscales . It consists of 35 items. Each item is valued on a Likert scale, 1 as very dissatisfied, 2 not very satisfied, 3 indifferent, 4 satisfied, 5 very satisfied. The global score is obtained by adding the values assigned to each item. A higher score means greater satisfaction.

Sociodemographic and obstetric data sheet. Prepared by the research team, it consists of sociodemographic data and variables related to childbirth.

Presentation of the birth plan to the hospital data sheet. It consists of four closed questions: received enough information on the pregnancy about the birth, presented the birth plan to the hospital, if not, what was the cause, a useful question of completion of the birth plan in the decision-making in the childbirth that was valued on a scale of 0 to 5, and a question if they would use the birth plan in the next pregnancy.

### **Data collection procedure**

The midwives of the ASSIR will carry out the recruitment of the pregnant women in the control and intervention group in the prenatal visit of 24-28 weeks of gestation and they will be explained what the study consists of verbally and in writing. If they wish to participate, the informed consent will be collected and then the midwife will collect the sociodemographic and obstetric data and will deliver the birth plan for the pregnant women to fill in at home.

In the prenatal visit of 29-33 weeks of gestation, midwives will collect the completed birth plans and will deliver a new birth plan that the women will fill out at home and will be instructed to deliver a copy at the prenatal visit between the 34-40 weeks of gestation.

The midwife will keep a copy and will indicate to the pregnant women that the original must be presented to the hospital. In the women in the intervention group, the midwives will carry out the standardized counselling intervention in the preparation of the birth plan based on the shared decision making of Epstein et al and in the pregnant women in the control group, the midwives will carry out the usual practice of counselling the plan of birth.

In the postpartum visit between hospital discharge and the 6th postpartum week, the midwives of the control and intervention group will collect the childbirth data and deliver an sealed envelope with the questionnaire of questions about the childbirth and the birth plan, sufficient information satisfaction received during pregnancy about the delivery, usefulness of completing the birth plan, intention to use it in the next pregnancy and the MacKey questionnaire on the satisfaction of childbirth.

**Pilot test.** A pilot test will be carried out with 10 pregnant women in each ASSIR.

